#### Analysis of the primary endpoint

The formal test for difference in PFS between the two treatment arms will be done with a multivariate Cox regression analysis with adjustment for the stratification factor except hospital. The actuarial method of Kaplan and Meier will be used to estimate survival probabilities, while the Greenwood estimate will be used to construct corresponding 95% confidence intervals (CIs). Kaplan-Meier curves will be generated to illustrate PFS, for all patients as well as by treatment arm. A prespecified subgroup analysis will be performed for the following subgroups: node-negative CRC, CRS of 0 to 1 points, and KRAS wild-type.

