**Methods:**

This is an open label multicenter RCT. A total of 230 patients with resectable CRLM without extrahepatic disease will be included. Only patients with a clinical risk score (CRS) of 0 to 2 are eligible, meaning: patients are allowed to have no more than two out of five poor prognostic factors (disease-free interval less than 12 months, node-positive colorectal cancer, more than 1 CRLM, largest CRLM more than 5 cm in diameter, serum Carcinoembryonic Antigen above 200 μg/L). Patients randomized to arm A undergo complete resection of CRLM without any adjuvant treatment, which is the standard of care in the Netherlands. Patients in arm B receive an implantable pump at the time of CRLM resection and start adjuvant HAIP chemotherapy 4–12 weeks after surgery, with 6 cycles of floxuridine scheduled. The primary endpoint is progression-free survival (PFS). Secondary endpoints include overall survival, hepatic PFS, safety, quality of life, and cost-effectiveness. Pharmacokinetics of intra-arterial administration of floxuridine will be investigated as well as predictive biomarkers for the efficacy of HAIP chemotherapy. In a side study, the accuracy of CT angiography will be compared to radionuclide scintigraphy to detect extrahepatic perfusion. We hypothesize that adjuvant HAIP chemotherapy leads to improved survival, improved quality of life, and a reduction of costs, compared to resection alone.

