## Background

Colorectal cancer (CRC) is the third most common cancer in the Netherlands. More than half of patients with CRC will eventually develop colorectal liver metastases (CRLM), of whom 25% have resectable disease at first presentation [1]. Most patients develop recurrent disease after curative intent resection of CRLM, which in about 50% of patients is confined to the liver [2]. A large phase III trial investigating perioperative systemic chemotherapy for patients with resectable CRLM found overlapping survival curves: 5-year overall survival (OS) was 51% with perioperative chemotherapy versus 48% with surgery alone (*p* = 0.34) [3, 4]. Therefore, resection without additional chemotherapy is currently the standard of care in the Netherlands and better adjuvant treatment is needed.

The risk of recurrence can be predicted with the clinical risk score (CRS) [5]. The CRS is the sum of five poor prognostic factors: disease-free interval less than 12 months, node-positive CRC, more than one CRLM, largest CRLM over 5 cm in diameter, and serum carcinoembryonic antigen (CEA) level above 200 μg/L. After assigning one point to each of the five risk factors, patients can be stratified into low-risk (0–2 points) and high-risk (3–5 points) of recurrence.

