### Study design

The PUMP trial is a phase III randomized controlled open label, multicenter trial to compare the combined efficacy of resection and/or open ablation and adjuvant HAIP chemotherapy to resection and/or open ablation alone in patients with CRC and resectable CRLM with a low CRS (0–2 points). This trial started in August 2018. Five centers participate in this study (Erasmus MC Cancer Institute, Rotterdam; Antoni van Leeuwenhoek, Amsterdam; Academic Medical Center, Amsterdam; Universitary Medical Center Utrecht, Utrecht; IJsselland Hospital, Capelle aan den IJssel). Patients will be randomized in a 1:1 ratio (Fig. 1) to resection of CRLM only (arm A), or resection of CRLM with adjuvant HAIP chemotherapy (arm B). Stratification factors will be center, number of CRLM (< 4 or ≥ 4 CRLM), and size of the largest CRLM (< 5 cm or ≥ 5 cm). Blinding is not feasible because of the nature of the intervention, including a visible subcutaneous pump. In patients who received preoperative chemotherapy for CRLM, the CRS values prior to start of preoperative chemotherapy should be used to determine eligibility. A computed tomography (CT) scan in (early) arterial phase of the liver is required prior to inclusion to determine whether intra-arterial catheter placement is technically possible. The multidisciplinary meeting should determine that complete resection of the CRLM is feasible. Resectability is defined as the opportunity to achieve an R0 resection with a sufficient liver remnant. Randomization will be performed preoperatively if the participant meets all the criteria.

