## Discussion

In this trail patients receive adjuvant HAIP chemotherapy without systemic chemotherapy. HAIP chemotherapy in MSKCC is always combined with concurrent adjuvant systemic chemotherapy. Adjuvant systemic chemotherapy is currently not recommended in Dutch guidelines for patients who underwent complete resection of CRLM, since no difference in OS was found in a large RCT [3, 4]. Some retrospective studies confirmed that adjuvant systemic chemotherapy has no impact on OS in patients with a low CRS [25–27].

A previous RCT from MSKCC, which compared patients who received adjuvant systemic 5-fluorouracil (5-FU) and HAIP chemotherapy with patients who received systemic 5-FU alone demonstrated a beneficial 2-years OS of 85% with HAIP versus 69% with 5-FU alone (*p* = 0.02) [10]. Despite this result, HAIP chemotherapy has not been widely adopted. The NCCN guidelines recommend adjuvant HAIP chemotherapy for CRLM as an option in experienced centers (Category 2B). A retrospective study from MSKCC demonstrated a superior OS of 23 months (67 months versus 44 months) in patients treated with HAIP and concurrent systemic chemotherapy compared to systemic chemotherapy alone in patients with resectable CRLM. These results have renewed interest in HAIP chemotherapy outside MSKCC [28]. Another phase III RCT is required to compare adjuvant HAIP chemotherapy for CRLM with surgery alone. The PUMP trial aims to definitively elucidate the efficacy of adjuvant HAIP chemotherapy in patients with resectable CRLM.

Only low-risk patients without EHD will be eligible for inclusion in the PUMP trial. This subgroup demonstrated to benefit more (median OS 89 months versus 53 months, *p* < 0.001) compared to high-risk patients (median OS 50 months versus 35 months, *p* < 0.001). Furthermore, no survival benefit was found in patients with EHD prior to or at time of resection (median OS 37 months versus 33 months, *p* = 0.92). These results have determined the study design and sample size calculation for the PUMP trial.

HAIP chemotherapy requires a well-trained large multidisciplinary team. A previous RCT investigating intra-arterial chemotherapy for CRLM, performed in 26 centers in Germany, was terminated early due to high complication rates [29]. Therefore, we comprehensively trained and proctored the five multidisciplinary teams participating in the PUMP trial. Moreover, a pilot study prior to the RCT has been conducted to confirm the safety and feasibility.

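### Primary Cox model omits centre, a randomisation factor, and the clinical risk score: the test is valid, but a one-sentence change could gain a little power

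*Protocol article*

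**What the plan says.** All references are to the protocol article.

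- **Randomisation.** Study design: "Stratification factors will be center, number of CRLM (< 4 or ≥ 4 CRLM), and size of the largest CRLM", cut at 4 metastases and at 5 cm. "Patients will be randomized in a 1:1 ratio", and "Five centers participate in this study".
- **Primary test.** Analysis of the primary endpoint: the formal comparison of PFS is a "multivariate Cox regression analysis with adjustment for the stratification factor except hospital". Hospital can only mean the centre factor, so number and size stay in the model and centre is removed. No reason is given.
- **CRS.** Background: "The risk of recurrence can be predicted with the clinical risk score (CRS"). Abstract, Methods: "Only patients with a clinical risk score (CRS) of 0 to 2 are eligible", so the score is known for each patient before randomisation. In the PFS analysis it appears only as a subgroup (0 to 1 points).
- **Planning.** Sample size calculation: HR 0.60, taken from a multivariable analysis of a non-randomised cohort of 779 patients; control median 17 months; 80% power; two-sided 0.05; 126 events; 230 patients.

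**The concern.** A trial that balances its arms within centres would normally analyse within centres too, or say why not. The usual reason for dropping centre is a large number of small sites. Here there are five, averaging 230/5 = 46 patients and 126/5 ≈ 25 events each, so separate baseline hazards are feasible.

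CRS raises a related question. It is a baseline score already in hand, and the planned covariates cover it only in part. Number enters at 4 or more, whereas CRS scores anything above one. Disease-free interval, nodal status and CEA do not enter at all.

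In a Cox model, leaving out prognostic covariates moves a non-null HR toward 1 relative to the HR conditional on them, and costs some power. The planning value of 0.60 is itself covariate-adjusted, although the article does not list the covariates. A lightly adjusted model may therefore target a slightly weaker effect than the one the trial was sized for. This is the only formal test of the primary endpoint, so even a small gain at no cost in patients is worth considering.

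**Working it through.** **1. The plan's own figures.** With (1.960 + 0.842)² = 7.849:

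- Freedman: events = ((1 + 0.60)/(1 − 0.60))² × 7.849 = 16 × 7.849 = 125.6, so 126. This matches the plan.
- Schoenfeld: 4 × 7.849/(ln 0.60)² = 120.3, so 121. With 126 events, Schoenfeld power at HR 0.60 is 81.8%.
- Patients: exponential PFS with medians 17 and 17/0.60 = 28.3 months, 36 months' accrual (A) and 12 months' further follow-up (F). The event probability is 1 − (e^(−λF) − e^(−λ(A+F)))/(λA) = 0.679 and 0.504, mean 0.591. Then 126/0.591 = 213.0, and 213.0/0.95 gives 225, close to the stated 230.

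Neither figure depends on whether centre or CRS is in the model.

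**2. What an attenuated HR would mean.** If the log HR shrinks to 95% of its planned size, the HR is 0.616. Schoenfeld power with 126 events is then 77.7%, and 139 events would be needed by Freedman.

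**3. Simulation.** 2,000 trials per scenario, 230 patients, blocked randomisation within centre × number × size, analysis at the 126th event, true conditional HR 0.60. All models are fitted to the same simulated trials. The Monte Carlo standard error of each power is about 0.9 points.

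The following are assumptions, because the documents give no figures: CRS 0/1/2 in 15/40/45%; centre shares 35/20/20/15/10%; among patients with CRS above 0, at least 4 CRLM in 12% and size at least 5 cm in 20%, each with HR 1.3; and the CRS and centre effects in the first two columns.

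| CRS HR per point | Centre SD (log hazard) | Planned: HR, power | + centre strata: power | + CRS: power | + both: HR, power | Change, both |
|---|---|---|---|---|---|---|
| 1.0 | 0 | 0.597, 80.5% | 79.1% | 81.0% | 0.595, 79.2% | −1.3 |
| 1.25 | 0.1 | 0.602, 79.4% | 78.7% | 80.1% | 0.595, 79.1% | −0.3 |
| 1.25 | 0.2 | 0.600, 79.4% | 78.3% | 79.7% | 0.592, 79.0% | −0.4 |
| 1.0 | 0.3 | 0.611, 77.4% | 78.3% | 77.7% | 0.600, 78.5% | +1.1 |
| 1.5 | 0 | 0.607, 77.9% | 77.0% | 80.7% | 0.596, 79.4% | +1.5 |
| 1.5 | 0.2 | 0.610, 77.2% | 77.3% | 79.5% | 0.595, 79.1% | +1.9 |
| 1.5 | 0.4 | 0.615, 77.6% | 78.5% | 79.9% | 0.592, 81.2% | +3.6 |
| 2.0 | 0.4 | 0.635, 71.5% | 73.2% | 76.7% | 0.597, 78.3% | +6.8 |

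Centre alone changes power by −1.4 to +1.7 points. CRS alone changes it by about 0 to +3 points, and by +5.2 in the last row. A separate run with no prognostic effects (1,000 trials, 218 patients) gave 80.8% as planned and 78.8% with both added, a loss of 2.0 points.

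**4. Validity.** At a true HR of 1, across the same scenarios, the planned model gives a mean HR of 0.997 to 1.007 and rejects in 4.6% to 5.2% of trials.

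**The case against.** The strongest reply is that nothing here is wrong. The exclusion of centre is stated openly and in advance, no other passage conflicts with it, and the sample size does not rely on it. A condensed article that gives no reason does not show that there was none. All of this stands, and it is why the point is an improvement and not a correction.

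A reader might also infer stronger things that the documents do not support:

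- **That the planned HR is biased or the test faulty.** The shift toward 1 is non-collapsibility: a model with fewer covariates estimates a more marginal HR. There is no shift under the null, and type I error is kept. Nor is the standard error materially too large. With CRS HR 1.6 and centre SD 0.4, 3,000 simulated trials gave a mean standard error of 0.182 against an empirical SD of 0.180.
- **That a loss of about 7 points is to be expected.** Under the patient mix above, this needs a doubling of hazard per CRS point together with large centre differences. At CRS HR 1.6 and SD 0.4 the same 3,000 trials gave 73.3% against 77.3%, a gain of 4 points.
- **That leaving out CRS breaks the design.** CRS is not a randomisation factor, eligibility truncates it to 0–2, and two of its five items are partly covered by the number and size terms.
- **That the protocol itself shows centre to be prognostic.** The Discussion says that "HAIP chemotherapy requires a well-trained large multidisciplinary team", but the context is complications and delivery of the pump treatment, and the five teams were trained and proctored. At most this suggests differences between centres within arm B, which separate baseline hazards would not address.
- **That the trial has no margin.** By Schoenfeld, 126 events give 81.8% power.

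**Conclusion.** The point holds as a cheap improvement. The primary model omits a factor used in randomisation, without a stated reason, and leaves unused a baseline score that the protocol itself regards as prognostic. The planned test is valid.

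Adding both factors is worth about 0 to 4 power points if their effects are moderate and about 7 only if they are extreme. It costs up to about 2 points if neither matters. Where the omitted factors carry weight, the planned model's HR moves from 0.60 to about 0.61 or 0.615 at moderate strength, and to 0.635 in the extreme case. The fuller model's own estimates average slightly below 0.60, so not all of the gap between the two models is attenuation.

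Most of the gain comes from CRS. For centre, the argument is consistency with the randomisation more than power. The direction is secure if the factors are prognostic. The size is not, because the documents give neither the strength of CRS within 0–2 nor any variation between centres.

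**What to change.** Before any outcome data are seen, replace the model sentence in Analysis of the primary endpoint, and match it in the SAP, with wording such as:

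> Cox model stratified by centre, with treatment, number of CRLM (<4/≥4), size of largest CRLM (<5/≥5 cm) and CRS (0/1/2) as covariates.

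Report the model without centre and CRS as a sensitivity analysis. Use CRS as scored for eligibility, since that value is fixed before randomisation in both arms. If the sponsor prefers to keep centre out, one sentence giving the reason would suffice.

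The cost is one sentence and no additional patients or data. The downside is up to about 2 power points if neither factor is prognostic. With the assumed centre shares, the smallest centre would still contribute about 0.10 × 126 ≈ 13 events, so stratification remains workable.

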### Secondary endpoints

Secondary endpoints include: OS (calculated from surgery until death from any cause; patients still alive at last contact are censored), hepatic PFS, safety, quality of life (EQ-5D + QCQ-C30), and cost-effectiveness. Furthermore, the pharmacokinetic profile of intra-arterial administration of floxuridine will be investigated in more detail. Moreover, we aim to identify predictive biomarkers (circulating tumor DNA) for the efficacy of HAIP chemotherapy. Finally, the accuracy of CT angiography will be evaluated compared to radionuclide scintigraphy to detect extrahepatic perfusion.

## Sample size calculation

A median PFS of 17 months was observed in 228 low-risk patients with resectable CRLM at Erasmus MC treated between 2000 and 2012, without EHD (consistent with arm A). In a multivariable analysis using a consecutive cohort of 779 low-risk patients without EHD, treated with or without HAIP chemotherapy between 2000 and 2012 at MSKCC, a hazard ratio (HR) of 0.60 (95% CI: 0.49–0.75) was found. Given a HR of 0.60 (corresponding to a median PFS of 28 months in arm B), 80% power and a 2-sided significance level α = 0.05, a total of 126 events need to be observed. With an expected accrual rate of 6 patients per month in five centers, 3 years accrual and one additional year of follow-up, and taking into account a drop-out rate of 5%, a total of 230 patients need to be randomized. No interim analysis is planned for survival outcomes.

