### Investigational procedures of the experimental arm (arm B)

The treatment of patients randomized to the experimental arm consists of HAI pump placement following complete resection and/or open ablation of all CRLM. Pump implantation will be cancelled in patients with unexpected unresectable CRLM or EHD detected at the time of surgery. Implantation of the HAI pump (Tricumed IP2000V infusion pump; Fig. 2) is performed by an open or minimal-invasive approach. In patients requiring simultaneous resection of the primary tumor and CRLM, the colorectal resection is performed after pump placement to reduce the risk of pump contamination. The implantation procedure of the infusion pump and dose adjustment protocols have been discussed by previous authors and was optimized for the materials used in this trial [14, 15]. In addition to local treatment of the CRLM, a cholecystectomy is performed to avoid cholecystitis as a result of inadvertent intra-arterial chemotherapy of the gallbladder [16]. The pump catheter is positioned in the gastroduodenal artery (GDA) allowing perfusion of the entire liver without obstructing the flow in the hepatic artery. The pump catheter has rings at the distal end that allow for securing the catheter with non-absorbable ties in the GDA (Fig. 3). In patients with abnormal hepatic arterial anatomy, the GDA is still the preferred site, as long as it connects with a proper hepatic artery perfusing at least one segment of the liver. Perfusion of the entire liver can be achieved in these patients by ligating all accessory and replaced hepatic arteries. Intrahepatic shunts will typically reassure that the catheter perfuses all liver segments.

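### The 80% power applies a hazard ratio from patients grouped by HAIP treatment, undiluted, to an arm formed before surgery in which some pumps may be cancelled

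*Protocol article*

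**What the plan says.** The Sample size calculation section gives every design input. The control arm rests on a local series: "A median PFS of 17 months was observed in 228 low-risk patients with resectable CRLM at Erasmus MC". The effect comes from a multivariable analysis of 779 low-risk patients without extrahepatic disease: "treated with or without HAIP chemotherapy between 2000 and 2012 at MSKCC, a hazard ratio (HR) of 0.60 (95% CI: 0.49–0.75) was found". The same figure is carried to the experimental arm, described as "corresponding to a median PFS of 28 months in arm B". The target is then set: "80% power and a 2-sided significance level α = 0.05, a total of 126 events need to be observed". The only allowance is 5% drop-out, giving 230 patients.

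Other sections determine who is in arm B. Under Study design: "Randomization will be performed preoperatively if the participant meets all the criteria". Under Investigational procedures of the experimental arm: "Pump implantation will be cancelled in patients with unexpected unresectable CRLM or EHD detected at the time of surgery". According to the Abstract, HAIP starts 4 to 12 weeks after the operation, and Postoperative procedures experimental arm requires liver perfusion to be confirmed before the first dose.

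The primary analysis is introduced as "The formal test for difference in PFS between the two treatment arms", using an adjusted Cox model. The article names no analysis set.

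**The concern.** The hazard ratio of 0.60 contrasts patients who had HAIP with patients who did not. The Background describes the centre's wider HAIP series as patients whose resection was complete. The trial arms are formed one step earlier, before it is known whether resection will be complete and whether a pump will be placed. A patient allocated to arm B whose pump is cancelled stays in arm B under an analysis by randomised arm, but cannot gain from HAIP. The average effect across arm B is then weaker than 0.60.

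The 5% drop-out does not address this. It adds patients so that 126 events are still reached, and it leaves the assumed effect unchanged.

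At stake is the reading of a null result. The article plans no interim analysis of survival and presents the trial as a definitive test. A negative finding would be judged against 80% power even if the power of the randomised comparison were lower.

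**Working it through.** **Inputs from the article:** hazard ratio (HR) 0.60; 80% power; two-sided 0.05; 1:1 allocation; control median PFS 17 months; 36 months of accrual plus 12 of follow-up; 5% drop-out. **Assumed:** the untreated share *u* of arm B, shown from 5% to 20%, with untreated patients at the control-arm hazard.

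**Step 1: reproduce the plan.** Freedman's formula is D = (1.960 + 0.842)² × [(1 + HR)/(1 − HR)]². At HR 0.60 this is 7.849 × (1.60/0.40)² = 7.849 × 16 = 125.6, so 126 events, which matches exactly. (Schoenfeld's formula gives 121.) The arm B median is 17/0.60 = 28.3 months, also as stated.

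**Step 2: look for a hidden allowance.** With exponential PFS and uniform accrual, the event probabilities are 0.679 in arm A and 0.504 in arm B, mean about 0.591. Then 126/0.591 ≈ 213, rounded up to 214, and 214/0.95 ≈ 226 patients, against 230 stated. The undiluted HR and the drop-out inflation account for nearly all of N.

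**Step 3: dilute the effect.** On the log scale, HR(u) = 0.60^(1 − u). Power at 126 events is Φ(√126 × (1 − HR)/(1 + HR) − 1.960). For u = 10%: HR = 0.60^0.9 = 0.631; 11.225 × 0.369/1.631 = 2.54; 2.54 − 1.96 = 0.58; Φ(0.58) ≈ 0.72.

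| Untreated share of arm B | Expected HR | Power, log-scale dilution | Power, simulation | Power, linear dilution | Events for 80% (log scale) |
|---|---|---|---|---|---|
| 0% | 0.600 | 80.1% | 81.4% | 80.1% | 126 |
| 5% | 0.616 | 76.2% | 76.9% | 75.0% | 139 |
| 10% | 0.631 | 71.8% | 72.6% | 69.3% | 154 |
| 15% | 0.648 | 67.0% | 67.2% | 63.3% | 172 |
| 20% | 0.665 | 61.9% | 59.9% | 57.1% | 194 |

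The simulation is a log-rank test stopped at the 126th event, with 218 patients (230 × 0.95, rounded down) and 6,000 runs per row. The linear column uses HR = (1 − u) × 0.60 + u.

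**Step 4: vary the prognosis.** Patients found unresectable at surgery may do worse than the average control patient. If 10% of both arms are such patients, with an assumed median PFS of 3 months, simulated power is about 68%.

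**The case against.** Several points on the other side stand.

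- **No analysis set is named.** The exclusion criteria under Study population include extrahepatic disease at the time of liver resection, and PFS runs from surgery. The full protocol may remove patients found ineligible or unresectable at operation alike from both arms. Dilution from cancelled pumps would then largely disappear, leaving only pumps placed but never used. The article does not say that this is done.
- **No frequency is given.** The cancellation rule says what happens, not how often. Arterial-phase CT, multidisciplinary review of resectability and a check that the catheter can be placed all screen against failure.
- **Non-start is inferred.** The article gives a start window, a perfusion check, and embolisation with re-testing. It does not describe patients who never start.
- **The cohort's definition of HAIP treatment is not spelled out.** If patients were classified by pump placement, those with unused pumps are already inside the 0.60.
- **The printed confidence interval is wide.** At its upper limit of 0.75, 126 events give only about 36% power by the same formula, so a shift from 0.60 to 0.63 lies well within the disclosed uncertainty.

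The last point does not remove the concern. Sampling error in an estimate is separate from whether the estimate refers to the right group, and dilution moves the expected effect in one direction only. Nor is this a detail left to a fuller document: the calculation is printed, and Step 2 shows little room in it for an unstated allowance.

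A reader might infer that the trial has 72% power, or that the protocol's own rules make 80% impossible. The documents support neither. The 72% belongs to an assumed 10% untreated, and a cancellation rule does not show how many patients it will affect.

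**Conclusion.** The concern holds as a mismatch between the effect-size input and the comparison of randomised arms. It is not an arithmetic error: 126 events is right for a hazard ratio of 0.60.

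Under a comparison of all randomised patients the direction is clear, and any untreated share of arm B lowers power below 80%. The size is unknown. Over an assumed 5% to 20% untreated, power falls from about 76% to about 62% with log-scale dilution, and from 75% to 57% with linear dilution. These figures rest on analysis by randomised arm, on untreated patients progressing at the control rate, and on 0.60 describing patients who were given HAIP. The loss is smaller if surgical exclusions are applied alike to both arms, or if the cohort counted patients by pump placement. It is larger if the untreated have a poor prognosis.

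**What to change.** In Sample size calculation:

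1. State that HR 0.60 refers to patients treated with HAIP, and that the primary comparison is of all randomised patients.
2. Give the expected HR and power at 126 events over a range of untreated shares, for example HR 0.63 and 72% power if 10% of arm B receive no HAIP. Use the proportion of non-starters from the pilot study mentioned in the Discussion, if it is available; the article does not report it.
3. Say that the 5% drop-out protects the number of events and does not cover this dilution.

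Keep N at 230. Do not recover power by dropping untreated patients from arm B: that would select one arm on what happened after randomisation.

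The cost is a few sentences and one recalculation, with no added patients or procedures. The change does not raise the trial's power. It makes the stated power match the comparison that will be made, and the figure may be less favourable.
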